## Abstract

**Methods::**

We will collect clinical data from 15 multi-center Korean medical clinics that treat FGID as part of an observational study registry. Patients who meet the criteria will be added to the registry after screening. They will receive a maximum 4-week treatment, and they will respond 3 times to a series of questions. We will investigate how doctors of FGID patients with diverse disease patterns choose the acupoints, and we will use a machine learning technique to identify the best acupoints for treating FGID patients.

**Discussion::**

This will be the first multi-center observational registry study to assess how traditional Korean medical practitioners diagnose and treat patients in the real world. The findings will shed light on how traditional Korean medicine treats FGIDs and demonstrate the rationale for the diagnostic and acupuncture treatment flow.

## 1. Introduction

At least one-third of visits to gastroenterology clinics are for functional gastrointestinal disorders (FGIDs), such as functional dyspepsia (FD) and irritable bowel syndrome (IBS).^[1]^ More than two-thirds of people have seen a doctor in the past 12 months, 40% of patients use routine medications, and one-third have undergone potentially needless abdominal surgery for their symptoms, such as a hysterectomy or cholecystectomy.^[2]^ These illnesses affect quality of life (QoL) to a degree that is comparable to that of organic gastrointestinal (GI) disease and are costly to treat.^[3]^ Many patients with FGIDs search for alternative treatments.^[4]^

Acupuncture is a non-pharmacological intervention that has been widely used to treat patients with FGIDs.^[5]^ A previous meta-analysis of FGID patients who received acupuncture treatment found that acupuncture is strongly related to improved symptoms despite the moderate or low strength of evidence.^[6]^ According to a recent meta-analysis, FD patients who received acupuncture and conventional therapy had a reduction in their symptom scores.^[7]^ Comparative Chinese trials have revealed that patients experience benefits from acupuncture compared to antispasmodic medications, despite randomized controlled trials showing no benefit of acupuncture compared to a credible sham acupuncture control for the severity or QoL of IBS symptoms.^[8]^ Patients with FD who have postprandial discomfort syndrome respond more favorably to acupuncture, particularly at certain acupoints along the stomach meridian.^[9]^ However, no prospective observational study has collected real-world data to determine the best acupoints for treating FGID patients.

The fourth version of the Rome Foundation criteria was released in 2016 and is used to diagnose and categorize FGIDs. Rather than identifying and addressing particular underlying pathophysiological mechanisms, the current methods of treating FGIDs focus on the most common GI and psychological symptoms.^[3]^ However, pattern identification is a technique used in complementary and alternative medicine sectors, such as traditional Korean medicine, to diagnose patients with FGID and reveal the precise pathophysiological pattern of the disease (diagnosis). Doctors offer patients several forms of acupuncture treatment at the outpatient department of a Korean medical clinic following the patients’ patterns.^[10]^ Significant factors have been discovered that may be used to predict the effectiveness of acupuncture for patients with FD using machine learning and support vector machine methods.^[11]^ Nonetheless, few studies have been performed on acupuncture treatment based on a pattern identification diagnosis of FGIDs.^[12]^

We have designed an observational registry study including 15 Korean medical clinics. We will investigate the pattern of acupoint selection for FGID patients with various disease patterns, and further determine the best acupoints for treating FGID patients using a machine-learning algorithm.

## 2. Methods

### 2.1. Study registration

The Clinical Research Information Service of the Korea National Institute of Health, Republic of Korea, received registration for this study (KCT0008145).

### 2.2. Study design

Up to 420 patients with a doctor-diagnosed FGID will participate in this multi-center, prospective observational registry study. This study will be conducted in 15 traditional Korean medical clinics located in the Republic of Korea. All subjects will be recruited from the daily outpatient department of each clinic participating in the study.

First, using various methods of pattern identification, we will investigate the acupoint selection patterns that doctors recommend for patients with FGIDs. Patients with FGIDs will receive a pattern identification questionnaire. Second, we will determine which acupoints are best for treating FGID. A machine learning method will be used to extract the combinations of acupoints to predict the acupuncture responders. Patients included in the study will complete a series of questionnaires a maximum of 3 times throughout their treatment period: at the first appointment (week 0), 2 weeks later (week 2), and 4 weeks later (week 4).

After receiving an explanation of the advantages and disadvantages of participating in the study, the patients will be requested to sign an informed consent form in writing during their initial appointment. They will be assessed for compliance with the inclusion and exclusion criteria in a screening procedure. Eligible subjects will be added to the registry after screening. The patients will receive combined Korean medical treatment for a maximum of 4 weeks, which will include acupuncture treatment and the responses to a series of questionnaires. The detailed study procedure is shown in Figure 1.

**Figure 1. F1:**
[figure not shown]
SPIRIT figure showing the schedule of enrollment, interventions and assessments. AES = acupuncture expectancy scale, FD-QoL = functional dyspepsia quality of life, IBS-QoL = irritable bowel syndrome quality of life, NPI = Nepean Dyspepsia Index, STPI-FD = standard tool for pattern identification of functional dyspepsia.

### 2.3. Participants

Adults aged 18 to 70 years will be the subjects of this registry study. Following a thorough description of the study purpose and procedures, participants will sign a written consent form.

#### 2.3.1. Inclusion criteria.

Patients diagnosed with FD (either epigastric pain syndrome or postprandial distress syndrome) or IBS via the Rome Ⅳ Criteria, who can consistently visit a clinic for treatment, and who voluntarily agree to participate will be included in the study.

#### 2.3.2. Exclusion criteria.

The following patients will be excluded: those with an organic disease that induces dysfunction of the GI tract (e.g., central nervous system disease, neoplastic disease, metabolic disease, inflammatory disease of the GI tract, or taking medicine that affects GI tract function), who have received active treatment (e.g., hospitalization for severe FGID symptoms) within 3 months before visiting the outpatient Korean medical clinic, and who have participated in other studies. In addition, patients who are considered inappropriate to participate, based on the decision of the doctor, will also be excluded.

#### 2.3.3. Recruitment of the study participants.

All adult patients seeking treatment for FGID at the outpatient division of any of the 15 participating Korean medical clinics will be eligible to join the patient group. Each clinic will receive a supply of posters with advertisements. These posters will be used to inform visiting patients.

#### 2.3.4. Registration of participants.

FGID patients who match the requirements will be added to the registry. The medical data of the participants related to FGID will be collected during their medical care after they have enrolled in the registry.

#### 2.3.5. Pattern identification types of patients.

Patients will be categorized into 6 pattern identification types, as per the clinical practice guideline of Korean medicine for FD: spleen and stomach deficiency and cold pattern; spleen deficiency with qi stagnation pattern; liver-stomach disharmony pattern; tangled cold and heat pattern; pattern of dampness and heat in the spleen and stomach systems; and food retention pattern. The Standard Tool for Pattern Identification of Functional Dyspepsia (STPI-FD) questionnaire will be employed to determine the patient pattern.^[13]^ This questionnaire consists of 12 categories of questions reflecting various symptoms of FGIDs. This questionnaire will be presented to patients only once at the first visit (0 weeks).

### 2.4. Intervention

Acupuncture will be used to treat all FGID patients as determined by the doctor. Patients may receive extra treatment depending on the doctor decision.

#### 2.4.1. Acupuncture treatment.

Based on the top 10 frequently used acupoints according to previous systematic reviews, examples of acupoints (e.g., CV12, ST25, ST36, CV10, LR3, BL20, PC6, GV7, BL21, and SP6) will be shown in the case report form. Pattern identification will be used to choose the acupoints, and more acupoints will be permitted based on the patient additional symptoms. There will be no restrictions on the number of acupoints used for treatment. Korean medical experts with at least 5 years of clinical practice will deliver all acupuncture treatments.

#### 2.4.2. Other co-interventions.

Herbal acupuncture, herbal medicine, cupping therapy, moxibustion, and other treatments will also be provided simultaneously in clinics in addition to traditional acupuncture. Co-interventional data will be considered a covariate when estimating the impact of the treatment.

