### 2.6. Sample size and data analysis

Although sample size calculations are not necessary for observational registry studies, we have determined that 420 individuals are needed, considering the volume of business at the outpatient clinics taking part in this study.

Each outcome measure will be compared to the clinical outcome between the baseline and termination, and the clinical outcome will be a dependent variable. Combinations of the applied acupoints will act as independent factors to predict the most effective acupoints for the acupuncture treatment. To improve the effectiveness of acupuncture treatments for FGID patients, the properties of the acupoints will be extracted using machine learning algorithms, such as support vector machine and logistic regression models.

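### Section 2.4.2 adjusts for co-interventions without separating those chosen at week 0 from later additions, so part of the covariate may be a consequence of early response

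*Protocol article*

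**What the plan says.** Four places in the protocol article bear on this.

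- Section 2.4.2 names the adjustment: "Co-interventional data will be considered a covariate when estimating the impact of the treatment". This is the only variable the article calls a covariate. No time window is attached.
- The same section says that herbal medicine, cupping, moxibustion and "other treatments will also be provided simultaneously in clinics in addition to traditional acupuncture". Section 2.4 adds: "Patients may receive extra treatment depending on the doctor decision".
- Section 2.2 sets the period: "The patients will receive combined Korean medical treatment for a maximum of 4 weeks". Questionnaires fall at weeks 0, 2 and 4.
- Section 2.6 gives the model. On the outcome: "Each outcome measure will be compared to the clinical outcome between the baseline and termination, and the clinical outcome will be a dependent variable". On the predictors: "Combinations of the applied acupoints will act as independent factors to predict the most effective acupoints for the acupuncture treatment".

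**The concern.** A covariate used for adjustment should be fixed before the treatment can act on it. Co-interventions chosen together with the acupoints at the first visit meet that test. A co-intervention added later because the patient has not improved does not. It partly reflects the early response, and the acupoints influence that response. The sentence in 2.4.2 covers both kinds.

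Two distortions follow for the later kind. An add-on with no effect acquires a negative coefficient, because it marks poor responders. An effective acupoint loses part of its estimated effect, because its patients improve and attract fewer add-ons. The study aims to find the best acupoints, so bias in their coefficients matters. A larger sample would not remove it.

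**Working it through.** The article gives no effect size, SD, correlation or share of response-driven additions, so every input here is an assumption. Its 420 patients come from clinic volume; there is no stated calculation to reproduce.

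**Identity.** Let A be the acupoint, C the add-on and Y the improvement at week 4. In least squares, unadjusted effect of A = adjusted effect of A + γδ. Here γ is the coefficient of C and δ is the difference in add-on use between patients with and without A. If a fraction q of add-on decisions follows early response, γ and δ both scale roughly with q. The false harm therefore grows like q and the loss in the acupoint effect like q².

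**Threshold model.** Assume the following:

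- A is given to half the patients, independently of prognosis.
- Its effect is 0.4 at week 2 and 0.5 at week 4, with within-group SD 1 and week-2/week-4 residual correlation 0.6.
- C is inert and given to half the patients. A fraction q of decisions goes by below-median week-2 response; the rest are random.

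The week-2 median lies about 0.2 from each group mean, with Φ(0.2) = 0.579 and φ(0.2) = 0.391. Then:

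- δ = −q(2 × 0.579 − 1) = −0.158q
- γ = −q × 0.6 × 0.391 / [0.25 − (0.079q)²]
- adjusted effect of A = 0.50 − γδ

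| q | γ | loss γδ | adjusted A | simulated A; C |
|---|---|---|---|---|
| 0.25 | −0.235 | 0.009 (2%) | 0.491 | 0.490; −0.234 |
| 0.50 | −0.472 | 0.037 (7%) | 0.463 | 0.462; −0.471 |
| 1.00 | −0.963 | 0.153 (31%) | 0.347 | 0.349; −0.959 |

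Without C in the model, the simulated acupoint effect is 0.50 at each q.

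**Graded model.** Here the log-odds of an add-on rise by s = 1 or 2 per SD of poorer week-2 response, the residual correlation is r = 0.5 or 0.7, and the acupoint effect is 0.5 at both times. With every decision response-driven:

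| r, s | adjusted A | C |
|---|---|---|
| 0.5, 1 | 0.456 | −0.42 |
| 0.5, 2 | 0.408 | −0.61 |
| 0.7, 1 | 0.441 | −0.58 |
| 0.7, 2 | 0.371 | −0.85 |

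The loss is 0.044/0.5 = 9% to 0.129/0.5 = 26%. Scaling the two extreme rows gives:

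- **q = 0.25:** C from 0.25 × (−0.42) = −0.105 to 0.25 × (−0.85) = −0.21. Loss from 9%/16 = 0.6% to 26%/16 = 1.6%.
- **q = 0.50:** C from −0.21 to −0.425. Loss from 9%/4 = 2% to 26%/4 = 6.5%.

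Direct simulation at these shares gives −0.10 to −0.42 for C.

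**At 420 patients.** The standard error of γ is about 2/√420 = 0.098. Under the threshold model at q = 0.25, z = 0.235/0.098 = 2.4. In 2,000 simulated trials the inert add-on was significantly harmful in 68% at q = 0.25 and in nearly all at q = 0.50. Under the graded model at q = 0.25, z lies only between 0.105/0.098 = 1.1 and 0.21/0.098 = 2.1.

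**Order of points.** The loss for a point is roughly proportional to its early effect. If all points act at the same speed, they shrink by nearly the same factor: five points with effects 0.5, 0.35, 0.2, 0.1 and 0 kept their order in all four graded scenarios. Now take effects of 0.50 (early effect 0.4) and 0.45 (early effect 0.1) in the threshold model. At q = 1 the losses are about 0.153 and 0.153 × 0.1/0.4 = 0.038. The estimates are 0.35 and 0.41, so the order reverses. At q = 0.50 they are 0.463 and 0.45 − 0.009 = 0.441, and it does not.

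**Contrast cases.** If an active add-on (+0.3) is packaged with the acupoint at visit 1, the unadjusted estimate is 0.59 and the adjusted one 0.50, so adjustment is right. If an active add-on (+0.3) is given later and wholly by response, the unadjusted estimate is 0.50 − 0.3 × 0.158 = 0.45. That is a total effect; the direct effect is 0.50.

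**The case against.** The strongest reply is that the article never says co-interventions are added because of poor response. It describes combined care given alongside acupuncture, and the pattern questionnaire that categorises patients is given once, at week 0. If co-interventions are part of the first-visit package, adjusting for them is correct. This stands in part: the mechanism is permitted and not documented, so its frequency is unknown. But giving treatments alongside acupuncture does not fix their start at visit 1, and section 2.4 leaves additions open.

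A second reply is that coding and time window belong in an analysis plan, which is not shown. Such a plan could narrow the sentence. As it stands, 2.4.2 commits to the covariate without restriction, and the remedy changes what is adjusted for.

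A third is that the stated aims concern acupoint selection and responder prediction. A false coefficient for a co-intervention then harms only if someone reports or interprets it. That lowers the weight of the more robust distortion.

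A reader might also infer that acupoint effects will be 9–26% too small, or that the ranking will be distorted. Neither follows. The first needs every addition to be response-driven. The second needs points that act at different speeds as well.

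**Conclusion.** The point holds in a limited form. Section 2.4.2 allows adjustment for a variable that may partly result from early response. The direction of the bias is clear for an inert, response-driven add-on; its size in this registry cannot be known from the article. With 25–50% of decisions response-driven, the false harm is about 0.1 to 0.4 SD under a graded trigger and up to 0.47 SD under a sharp one, while acupoint attenuation stays at about 0–7%. Only if all decisions are response-driven does attenuation reach 9–26% (about 30% under the sharp trigger) and the false harm 0.85 SD (0.96 SD).

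These figures assume a single inert add-on given to half the patients and an acupoint chosen independently of prognosis. The results do not mean that co-interventions should be left out altogether: those chosen at week 0 are proper covariates. The point is worth acting on because the correction is cheap and the start dates may not be recoverable later.

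**What to change.** In section 2.4.2, define the adjustment covariate as the co-interventions prescribed at week 0. Record a start date on the case report form for each co-intervention begun later. Report later additions descriptively, for example by pattern and clinic, or in a sensitivity analysis such as time-varying weighting that uses the week-2 score. Do not enter them as ordinary covariates. State that the main estimate is the total effect of the acupoints plus whatever usual add-ons follow.

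The cost is a few sentences of analysis text and one date field per co-intervention. The change concerns recording and analysis only and alters no patient's care. The price is in interpretation: if later add-ons are active, the total effect differs from the direct effect of the acupoints (0.45 against 0.50 in the extreme case above). Confounding by baseline severity is a separate matter that this change does not settle.

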### 2.5. Outcomes

The Rome IV criteria will be used first to diagnose FGID. Patients who are assigned to this registry will be required to complete 3 evaluations of the Korean versions of the Nepean Dyspepsia Index,^[14]^ FD-QoL,^[15]^ and IBS-QoL questionnaires.^[16]^ The Nepean dyspepsia index questionnaire includes 15 questions on different dyspepsia symptoms that assess their frequency, seriousness, and subjective perception. Total of 21 questions divided into four areas, including nutrition, vitality, emotions, and social function, in FD-QoL questionnaire reflect how the QoL of FD patients has changed. In all, 34 items on how the QoL of IBS patients has changed are included in the IBS-QoL questionnaire. In addition, the acupuncture expectancy scale will be evaluated at baseline to gauge the general effects of treatment.^[17]^

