Next, the best acupoints for treating FGID with acupuncture will be predicted using machine learning and the patient results. Individuals respond to acupuncture in different ways.^[18]^ As mentioned above, machine learning can be used to forecast the best acupoints based on patient outcomes. In a previous study, the effectiveness of acupuncture was predicted using a support vector machine for individuals with FD.^[11]^ Gender, disease subtype, and education level were significant predictors of treatment results. Similarly, machine learning will be used to identify those who are more likely to respond to acupuncture, or those who will improve (display minimally clinically significant differences) from baseline following 4 weeks of acupuncture treatment. Data from 80% of the patients with FD will be used to create a predictive model, and the data from the other 20% will be used to validate the model and assess its performance. The performance of supervised machine learning models, such as support vector machine and logistic regression models, will be assessed using accuracy, sensitivity, and specificity analyses. Machine learning can be used to predict the optimal acupoints for each patient and help doctors assess treatment responses.

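### The registry enrols FD or IBS patients and promises an answer for FGID, but the only predictive model described is built and tested on FD patients, so it supports no predictive conclusion for IBS patients without FD

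*Protocol article*

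**What the plan says.** **Who is enrolled.** Section 2.3.1 admits "Patients diagnosed with FD (either epigastric pain syndrome or postprandial distress syndrome) or IBS via the Rome" IV criteria, so a patient with IBS and no FD is eligible. Section 2.2 sets the size: "Up to 420 patients with a doctor-diagnosed FGID will participate in this multi-center, prospective observational registry study". No division between FD and IBS is given. Section 2.6 bases the number on clinic throughput: "we have determined that 420 individuals are needed, considering the volume of business at the outpatient clinics taking part in this study".

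**What is promised.** The Introduction says the study will "further determine the best acupoints for treating FGID patients using a machine-learning algorithm". The Abstract, sections 2.2 and 2.6, and the opening of the Discussion state the aim for FGID in the same way.

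**What is measured.** Section 2.5 states: "Patients who are assigned to this registry will be required to complete 3 evaluations of the Korean versions of the Nepean Dyspepsia Index". The sentence goes on to name FD-QoL and IBS-QoL, so every patient completes all three questionnaires. Section 2.6 adds: "Each outcome measure will be compared to the clinical outcome between the baseline and termination". For the pattern diagnosis, section 2.3.5 states: "The Standard Tool for Pattern Identification of Functional Dyspepsia (STPI-FD) questionnaire will be employed to determine the patient pattern".

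**What is modelled.** The Discussion contains the only description of model construction and validation: "Data from 80% of the patients with FD will be used to create a predictive model", with the other 20% used to validate it. A responder is a patient who reaches a minimal clinically significant improvement after 4 weeks. The instrument is not named.

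**The concern.** The population promised an answer and the population in the model differ. If the Discussion is taken literally, IBS patients without FD contribute nothing to the model, and a statement about the best points for FGID would rest on FD data alone. The effective sample would also be smaller than the registry total, by an amount the article does not allow a reader to work out.

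If the FGID wording is taken literally instead, all patients enter one model, and the definition of response becomes critical. The only symptom scale collected is a dyspepsia scale. IBS patients without dyspepsia may have less room to improve on it. Section 2.4.1 lets doctors add points for additional symptoms, so point use may well differ by diagnosis. Diagnosis could then confound the relation between points and response. What is at stake is whom the predictive result covers and, under pooling, whether some points are wrongly ranked as ineffective.

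**Working it through.** **1. Passages side by side.**

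| Topic | Population | Place |
|---|---|---|
| Eligibility | FD or IBS | 2.3.1 |
| Aim of the prediction | FGID | Introduction, 2.2, 2.6, Discussion |
| Outcome questionnaires | all registrants, all three instruments | 2.5 |
| Model training and validation | FD | Discussion |

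The second and fourth rows cannot both define the modelling population. No IBS model is described anywhere in the article.

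**2. The plan's own figure.** No formula reproduces 420, because it comes from clinic volume. The only arithmetic available is 420 / 15 = 28 patients per clinic.

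**3. Sample behind an FD-only model.** Let s be the share of registrants with FD, including those who also have IBS. The article gives no value, so s is assumed. FD patients = 420 × s; training = 0.8 × FD; validation = the rest.

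| s (assumed) | FD | Training | Validation | Outside the model |
|---|---|---|---|---|
| 90% | 378 | 302 | 76 | 42 |
| 70% | 294 | 235 | 59 | 126 |
| 50% | 210 | 168 | 42 | 210 |

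**4. If all were pooled on a dyspepsia-based response, ignoring diagnosis.** Take an acupoint with no true effect. Assumed inputs, none from the article: 30% IBS-only; the point used in 70% of IBS-only and 30% of FD patients; response 50% in FD and p in IBS-only.

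- Users: FD 0.70 × 0.30 = 0.21; IBS-only 0.30 × 0.70 = 0.21. IBS-only share = 0.21 / 0.42 = 0.500.
- Non-users: FD 0.70 × 0.70 = 0.49; IBS-only 0.30 × 0.30 = 0.09. IBS-only share = 0.09 / 0.58 = 0.155.
- Spurious difference (users minus non-users) = (0.50 − p) × (0.155 − 0.500) = −0.345 × (0.50 − p).

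| p, IBS-only response | Users | Non-users | Spurious difference |
|---|---|---|---|
| 5% | 27.5% | 43.0% | −15.5 points |
| 10% | 30.0% | 43.8% | −13.8 points |
| 20% | 35.0% | 45.3% | −10.3 points |
| 30% | 40.0% | 46.9% | −6.9 points |
| 50% | 50.0% | 50.0% | 0 |

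The other inputs matter too. At p = 5%, an IBS-only share of 20% gives −12.2 and 40% gives −17.4. At a 30% share and p = 30%, narrowing point use to 50% versus 30% gives −3.6. With equal use in both diagnoses the difference is exactly zero.

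**The case against.** The strongest reply is that the pooled analysis in step 4 is not in the article. The only stated model population is FD, no passage makes a dyspepsia scale the response for IBS patients, and every input to that calculation is assumed. Treating diagnosis as a predictor, fitting models by diagnosis, or using IBS-QoL for IBS would all be compatible with the text and would address the problem. This stands: the pooling bias is a conditional risk, not an established flaw.

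A second reply is that this is a condensed article. Naming the response instrument for each diagnosis and giving expected subgroup counts are details that a full protocol or analysis plan may hold. That also stands, so their absence is not the point here. The printed conflict between an FGID aim and an FD model is a different matter, because it is stated rather than omitted. The Discussion may say FD loosely, since it has just cited an earlier FD study, but the reader cannot tell.

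A reader might infer more than the text supports:

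- *That IBS patients are assessed only with dyspepsia instruments.* They are not: section 2.5 gives everyone the 34-item IBS-QoL.
- *That IBS patients drop out of the results altogether.* They remain in the first aim, the description of acupoint selection, and in the baseline-to-termination comparisons of section 2.6. Patients with both FD and IBS would be in the FD model.
- *That IBS patients cannot improve on the dyspepsia scales.* The article gives no baseline scores and no figure for overlap between the diagnoses.
- *That the pattern tool misclassifies IBS patients.* Section 2.3.5 says its questions reflect FGID symptoms, while the Discussion describes a test that distinguishes types of FD. Its use in IBS-only patients is at most a caveat.

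**Conclusion.** The contradiction holds and is confined to the predictive aim. As written, the model is trained and validated on FD patients and supports no predictive conclusion for IBS patients without FD. Its sample is the FD share of up to 420, which the article does not state; assumed shares of 90% to 50% give 378 to 210 patients. This conclusion needs no assumption beyond the text; only the counts do.

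The pooling bias is secondary. It arises only if response is defined on a dyspepsia scale, response and point use both differ by diagnosis, and diagnosis is not accounted for. Under the inputs of step 4 it runs from about −7 to −16 points as IBS-only response falls from 30% to 5%. It vanishes if response or use is equal across diagnoses.

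**What to change.** Reconcile the modelling paragraph of the Discussion with the Introduction and sections 2.2 and 2.6, before any model is fitted, in one of two ways:

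1. Keep the FD-only model and limit the predictive conclusion to FD wherever it is now stated for FGID. IBS patients stay in the description of acupoint selection and in the before-after comparisons.
2. Fit and validate separate FD and IBS models, with a response matched to the diagnosis: the Nepean Dyspepsia Index for FD and IBS-QoL for IBS. For patients with both, report both.

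Under either option, state how many patients of each diagnosis stand behind each model. Any STPI-FD pattern result in IBS-only patients is best labelled exploratory.

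The change is to wording and analysis only, since all the questionnaires are already planned. The first option narrows the claim. The second leaves fewer patients per model, and the IBS response would rest on quality of life because no bowel-symptom scale is collected.
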